#### Medicine treatment

Patients will receive donepezil hydrochloride 5 mg daily for 12 weeks. During the trial, participants will be prohibited from using other medicines for AD. The test drug was allocated based on the random coding sequence of the test drug and the number of cases. Each research unit will have a trial medication administrator. The investigator will screen qualified participants. After informed consent and writing of the study medical record, the trial medication administrator will arrange participants based on the order of patient visits and drug coding from small to large distributed medicines; further, they will be registered in the “Clinical Trial Drug Use Record Form.”

#### Follow-up

All participants will be treated for 12 weeks. Subsequently, they will enter a 24-week follow-up period. In the 24th and 36th weeks, the patients will be reassessed using the MMSE, Alzheimer’s Disease Cooperative Study-Activities of Daily Living (ADCS-ADL) scale, and Quality of Life-Alzheimer’s Disease (QOL-AD) scale.

### Outcome measures

Efficacy scores are performed by clinical neurologists and psychiatrists, who are trained by Shanghai Mental Health Center. Each time the scoring is performed by two scorers separately, if their results are inconsistent, the third scorer will make a ruling. All raters do not know the group of patients at the time of scoring. Table 2 shows the intervention and assessment time points to be used during the study period.

**Table 2 Tab2:**
[figure not shown]
Outcome measurements at each time-point

*Abbreviations*: *ADAS-cog* Alzheimer’s Disease Assessment Scale-Cognitive Subscale, *MMSE* Mini-Mental State Examination, *ADCS-ADL* Alzheimer’s Disease Cooperative Study-Activities of Daily Living, *QOL-AD* Quality of Life-Alzheimer’s Disease

#### Basic characteristic variables

The information questionnaire will be used to collect information such as age, gender, educational background, marital status, previous history, disease course, and MMSE scores. Furthermore, participants will undergo pre-intervention blood tests to test for amyloid precursor protein, apolipoprotein E4, and presenilin-1, as well as magnetic resonance imaging (MRI) scans for definitive diagnoses. A nurse will measure and record the patient’s vital signs.

#### Primary outcome measure

The ADAS-cog evaluated at week 12 (the end of intervention) is the primary outcome of the study. The scale contains 40 items and is used to assess the severity of cognitive-behavioral impairment in patients with AD [42]. In this trial, we choose the Chinese version of the ADAS-cog scale, which contains 12 items [43, 44]. The total score of the scale ranges from 0 (no error or damage) to 75 (severe damage). A higher score indicates a more severe cognitive impairment. Generally, individuals without AD or other dementia types have a score of 5.

#### Secondary outcome measures

##### ADAS-cog at follow-ups

Participants’ cognitive function will also be assessed using the ADAS-cog scale at week 24 (follow-up) and week 36 (follow-up).

##### ADCS-ADL

The ADCS-ADL scale is mainly designed to evaluate activities of daily living in patients with dementia. Currently, the most commonly used ADCS-ADL was developed by Lawton and Brody in 1969, which is divided into physical self-maintenance and instrumental activities of daily living scales. It contains 19 domains related to making phone calls, shopping, preparing meals, doing housework, washing, using transportation, taking medicine, and taking care of money [45]. The maximum ADCS-ADL score is 54. The higher the score, the better the patient’s quality of life related to cognition. Participants will be assessed using the ADCS-ADL at baseline, week 12(the end of intervention), week 24 (follow-up), and week 36 (follow-up).

##### MMSE

The MMSE was designed in 1975 as a screening tool for patients with dementia and psychiatric disorders. It is comprised of two parts: the first evaluates direction, memory, and attention, while the second part assesses naming capabilities, execution of oral and written commands, spontaneously writing sentences, and copying complex polygons. The items are rated on correctness or error (0, wrong; 1, right) with the outcome being the total number of correct responses. The maximum MMSE score is 30 and the test is not timed [46]. MMSE scoring standards are associated with education level. A score ranging from 27 to 30 is considered normal. The MMSE will be measured at baseline, week 12(the end of intervention), week 24 (follow-up), and week 36 (follow-up).

##### QOL-AD

The QOL-AD scale was developed in 1999 to evaluate the quality of life in patients with AD and their caregivers [47]. It is comprised of 13 items regarding physical and mental health, quality of life, social, and financial assessment. The response options are divided into four levels (1, poor; 4, excellent). The score ranges from 13 to 52 [48], with 52 indicating the highest quality of life. The QOL-AD will be measured at baseline, week 12 (the end of intervention), week 24 (follow-up), and week 36 (follow-up).

### Safety

The participants will be required to undergo the following necessary clinical laboratory tests for excluding any serious disease: blood routine, urine routine, and hepatic and renal functions during the screening stage and post-treatment (week 12). The results of the tests will be recorded to evaluate the safety of this trial. Treatment-related adverse events, including local hematoma, fainting, nausea, dizziness, insomnia, vomiting, or diarrhea, will be recorded in the CRF, including the time point, severity, measures taken, causal relationship with acupuncture treatment, and final outcome. Severe adverse events will be promptly reported to the principal investigator.

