The combined acupoints of HT7 and PC6 will be applied to patients with syndromes of heart qi deficiency, while KI3 and BL23 will be applied to patients with kidney essence deficiency syndrome.

The patient is in the supine position. After disinfection, disposable stainless steel needles (0.25mm×40mm) will be used to pierce the scalp or skin surface rapidly at a 15° angle on the head or 90° on the limbs and trunk. After the needle is inserted to the prescribed depth, the needle will be twisted for about 30s for a feeling of De Qi, such as sourness, numbness and heaviness. The patients will receive treatment 30 min per session, thrice per week (every other day) for 12 weeks. Meanwhile, electro-stimulation will be applied for GV20 and GV24 acupoints (2/50 Hz, dilatational wave). All treatment will be carried out by a well-skilled senior acupuncturist.

After each acupuncture treatment, the doctor will carefully observe whether the patient has pain, subcutaneous hematoma, and other discomfort. After the treatment, the patient will be observed in the clinic for 15 min.

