### Statistical methods

All statistical analyses will be performed using SPSS Statistics for Windows V21.0 (IBM SPSS). Three sets of data will be used:Full analysis test (FAS). This will include all randomized cases that underwent assessments at least once for efficacy analysis. Missing data, which may affect analysis, will be supplemented using the last observation data. FAS will be the main population for efficacy evaluation.The protocol set (PPS, per-protocol set). This will include patients that meet the inclusion criteria specified in the trial protocol, complete all observation period plans, and do not use other drugs or treatment measures that may affect efficacy evaluation during the trial period. Efficacy evaluation will be conducted using the FAS and PPS. PPS is a secondary population for efficacy evaluation.Safety analysis data set (SS, safety set). This will include all cases that use the study drug at least once and undergo post-treatment safety evaluation after randomization. The SS will be the main population for safety evaluation.

All statistical tests will be performed as two-sided, and the statistical significance will be set at *p*<0.05. Quantitative indicators will be described using the mean and standard deviation, maximum value, minimum value, and median; moreover, the classification indicators will be described using the number and percentage. For counting data, two-sample tests (including the Cochran-Mantel-Haenszel test) or Fisher’s exact probability method will be used for between-group comparisons; moreover, measurement data will be expressed as mean and standard deviation. One-way analysis of variance will be used for among-group comparisons; additionally, the least significant difference method (LSD-t test) will be used for between-group comparisons.

Demographics (age, sex, duration of illness, education level) and MMSE scores will be compared between the two groups as baseline assessments. The main time point for efficacy evaluation is 12 treatment weeks (for PPS), as well as when the group is discontinued (for the FAS population). The *t*-test will be used for between-group comparisons of other measured efficacy indicators, including analyzing the change from the baseline. The ADAS-cog, MMSE, ADCS-ADL, and QOL-AD will be analyzed using the covariance analysis model for between-group comparisons with the baseline.

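### Adverse-event recording is limited to treatment-related events with causality named for acupuncture only, and the safety set requires a later evaluation, so the between-arm safety comparison is open to bias

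*Protocol article*

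**What the plan says.** Safety section, recording: "Treatment-related adverse events, including local hematoma, fainting, nausea, dizziness, insomnia, vomiting, or diarrhea, will be recorded in the CRF". The details to be entered for each event end with "causal relationship with acupuncture treatment, and final outcome"; donepezil is not named.

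Safety section, other collection: "Severe adverse events will be promptly reported to the principal investigator", with no condition on relatedness. Blood, urine, liver and kidney tests are also recorded, the last two described as "hepatic and renal functions during the screening stage and post-treatment (week 12").

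Statistical methods, safety set: "all cases that use the study drug at least once and undergo post-treatment safety evaluation after randomization". The same paragraph adds: "The SS will be the main population for safety evaluation".

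Acupuncture treatment, per session: "After each acupuncture treatment, the doctor will carefully observe whether the patient has pain, subcutaneous hematoma, and other discomfort".

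Interventions and Medicine treatment give donepezil to both arms. Termination criteria foresee a patient stopping because of a serious adverse event or adverse reaction. Safety is part of the stated Objectives.

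**The concern.** Three stated rules bear on the comparison of harm.

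- Relatedness decides whether an event is entered at all. It would normally be an attribute recorded for every event.
- The only causality named is with a treatment that control patients do not receive, while the drug common to both arms has no attribution.
- Membership of the main safety population depends on something that happens after randomisation, namely a later safety evaluation. Patients who stop because of harm may be the ones who lack it.

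The Background cites evidence that acupuncture may reduce the side effects of medication, so the arm comparison of drug-type events is of direct interest. If events are filtered differently in the two arms, or affected patients leave the denominator at different rates, the reported difference reflects the collection rules as well as the treatments.

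**Working it through.** The article gives no adverse-event rate, safety-set size or safety power, so there is no figure to reproduce. The check sets the passages side by side and then illustrates the mechanisms with assumed inputs.

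**1. The recording rule.** Seven events are listed: local hematoma, fainting, nausea, dizziness, insomnia, vomiting and diarrhea. The Background names nausea, vomiting, diarrhea and insomnia as effects of Alzheimer's medicines, so 4 of the 7 can be expected in either arm. For a control patient the named causality question, relation to acupuncture, has no meaningful answer, and no question about donepezil is stated.

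Let r be the true risk, equal in both arms, and f_A and f_C the shares of events judged related in the acupuncture and control arms. The recorded difference is r × (f_A − f_C).

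| r (assumed) | f_A | f_C | Recorded, acupuncture vs control | Difference |
|---|---|---|---|---|
| 20% | 80% | 80% | 16% vs 16% | 0 points |
| 20% | 80% | 50% | 16% vs 10% | 6 points |
| 20% | 80% | 20% | 16% vs 4% | 12 points |
| 30% | 80% | 80% | 24% vs 24% | 0 points |
| 30% | 80% | 50% | 24% vs 15% | 9 points |
| 30% | 80% | 20% | 24% vs 6% | 18 points |

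Exchanging f_A and f_C reverses the sign.

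**2. The safety-set rule.** Two readings are open.

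- *Strict:* the required evaluation is the week-12 one, because that is the only post-treatment safety testing the article dates. A patient who stops early and misses it is excluded.
- *Looser:* any safety evaluation after the first treatment counts. A patient who stops early with a recorded event stays in, and only patients never evaluated are lost.

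Membership depends on a post-randomisation event under either reading.

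Let w be the share of affected patients who leave unevaluated, with all unaffected patients assumed to stay in. The risk seen in the safety set is r(1 − w) / (1 − rw).

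- r = 10%, w = 10%: 0.09 / 0.99 = 9.1%
- r = 20%, w = 25%: 0.15 / 0.95 = 15.8%
- r = 30%, w = 50%: 0.15 / 0.85 = 17.6%

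If r and w are the same in both arms, both risks are understated alike and a null difference stays null. A spurious difference needs w to differ. At r = 20%, w = 10% in one arm gives 0.18 / 0.98 = 18.4%, and w = 50% in the other gives 0.10 / 0.90 = 11.1%, a gap of 7.3 points.

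**3. How many patients could be lost.** The plan allows for 92 − 80 = 12 dropouts per arm; 15% of 92 is 13.8. Either is a ceiling for loss through dropout at the planned rate. It is reached only on the strict reading and only if no dropout has the required evaluation.

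**The case against.** The strongest reply is that this is a condensed article and its wording may be loose. A causality field would be largely redundant if only related events were entered, so the phrase may mean events on treatment. The listed events show that drug effects in controls were contemplated. Severe events are reported without a relatedness condition, and laboratory results are recorded. All of this stands, so it would be wrong to say that nothing but treatment-related events is captured. It does not supply a rule for ordinary events or an attribution to donepezil.

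The section on ethics approval and consent also says that data from patients who withdraw will be analysed. That statement concerns the outcome analysis and leaves the safety-set definition as it is.

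Several stronger readings are tempting but not supported:

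- *Unblinded doctors apply the filter.* The Blinding section says that doctors and acupuncturists are unblinded, but the article does not say who judges relatedness.
- *Harm is looked for at 36 contacts in one arm and one in the other.* Three sessions a week for 12 weeks do give 36 observed sessions, but extra contact is inherent in an add-on design. How events are collected from controls between visits may be in the full protocol, and the assessment table is not reproduced here. The silence is no finding.
- *Early withdrawals for harm are omitted.* This follows only on the strict reading.
- *Acupuncture exposure does not count towards the safety set.* Since both arms take donepezil, this affects only a patient who was needled but never took a dose.
- *Severe and serious conflict.* The Safety section uses one word for reporting and Termination criteria the other for continuation. This is a wording point to tidy, since the second passage is not a reporting rule.

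**Conclusion.** The point holds in this form: recording is limited to treatment-related events, causality is named for acupuncture only although both arms take donepezil, and the main safety population carries an evaluation condition whose timing is ambiguous. These are stated rules, not details left out of an article.

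The between-arm safety comparison is open to ascertainment and selection bias. A reader might infer that it is biased by a known amount or in a known direction; the document does not support that. The illustrated gaps of 0 to 18 points from the filter, and 7.3 points from unequal exclusion, rest entirely on assumed risks and shares, and both vanish when the shares are equal across arms. The efficacy analysis is not affected.

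**What to change.** Make three changes of wording:

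1. Record every adverse event in both arms regardless of presumed cause.
2. Assess causality separately for donepezil and for acupuncture, the latter only where it was given.
3. Define the safety set as all randomised participants who received at least one donepezil dose or one acupuncture session, analysed by treatment received, with no post-treatment evaluation condition.

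Report events observed at acupuncture sessions separately, as descriptive data for that arm.

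Study status gives June 2022 as the expected end and the article appeared in August 2022, so data collection may be complete. In that case new CRF wording cannot recover events that were never entered. The sponsor should then at least adopt the new safety-set definition, attribute the recorded events to donepezil as well as acupuncture, and state the relatedness filter as a limitation of the safety comparison.

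The cost is somewhat more events to record and code. The safety-set change needs no new data.

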### Recruitment

Participants will be recruited from three hospitals in Shanghai using the internet and health newspapers. Scientific lectures about the prevention and treatment of Alzheimer’s disease will be held in community service centers. Further, participants will be invited to a fixed location to have face-to-face meetings with the research liaison for assessment with respect to the eligibility criteria. Patients who have not undergone MRI within three months will be re-examined. After receiving informed consent and writing of the study medical record, the patients will undergo baseline evaluation with venipuncture. The decision to include a patient will be based on the evaluation and inspection results. This study will include 184 patients.

### Allocation

#### Sequence generation

The central randomization method will be used. The random number is uniformly issued by a dedicated person from the Data Management Center of Longhua Hospital through the statistical software SPSS (IBM SPSS statistics version 22.0, USA) network. This can ensure the random allocation being concealed.

#### Allocation concealment mechanism and implementation

The dispensing sequence is sealed in a light-tight envelope with a unique identification number. The envelope will be sent to a dedicated investigator who will write who and when opened the envelope. This identification number will appear on all reporting forms as the participant’s code. During the research process, sequence generation and allocation, recruitment, TCM syndrome differentiation, acupuncture treatment, efficacy evaluation, data management, and statistical analysis will be independently performed by different research specialists.

### Blinding

In this study, due to the nature of the intervention, the doctors and acupuncturists will not be blinded due to the assignment of the group to the operation. The data evaluation will be conducted by two evaluators who did not know the grouping. Data collection and statistical analysis are performed by a third party. Therefore, except for the differences in treatment between the two groups, all participants will be treated as equally as possible. During the intervention, the acupuncturist's treatment and the assessment of the scale of the assessor will be carried out at different times to ensure that they cannot communicate with each other.

### Data collection and management

All data will be corrected by the assessor on Case Report Form (CRF), then be a double entry into the electronic management system by two dedicated persons. The evaluator and the data entry person sign a confidentiality agreement before the study, and the data cannot be leaked. The study sponsor should retain the CRF for 5 years after the end of the study.

#### Ethics approval and consent to participate

The study protocol and research consent were approved by the Longhua Hospital Ethics Review Committee (2018LCSY060), Huashan Hospital Ethics Review Committee (2018-434), and Mental Health Center Shanghai Ethics Review Committee (2018-72).

Before participating in any research-related interventions, each participant will provide written informed consent. Before signing the consent form, the participants will be informed of all research procedures, benefits, and risks. Moreover, the patients will be informed that participation in the project is voluntary and that they can withdraw at any time. The data collected by the patient before shedding will be included in the intentional analysis. Data obtained from participants who withdraw from the study will be included in the analysis for determining the outcome. None of the participants will receive the intervention before signing the informed consent.

#### Quality control

Prior to contributing to this study, all investigators are required to attend and pass training sessions, particularly, for assessing scales and disease diagnosis (by Shanghai Alzheimer’s Disease and Related Disorders Center) assessments will be performed by individuals blinded to the group allocation. Syndrome differentiation is done by an independent TCM physician in each hospital. The syndrome differentiation and acupuncture program training was provided by Longhua Hospital, Shanghai University of Traditional Chinese Medicine.

### Oversight and monitoring

#### Data monitoring

Electronic data management system was developed by the Institute of Basic Research of the Chinese Academy of Chinese Medical Sciences to collect and manage the data.

The Shanghai Municipal Science and Technology Commission will establish an expert group which independent from researchers and conduct annual assessments of the project. The project team establishes a 3-level supervision committee to regularly supervise the outcome assessments and data management

#### Protocol amendments

The Ethics Committee of Longhua Hospital Affiliated to the Shanghai University of Traditional Chinese Medicine will conduct random checks to ensure that the study meets protocol requirements. If there is any change in the research protocol, it will be reported to the ethics committee for approval and revised in time in the clinical registration protocol.

#### Dissemination policy

The results of this study will be published in a peer-reviewed journal. Participants can request a summary of the results.

#### Patient and public involvement statement

Patient and public are not involved in the trial design and conduct. There is also no plan for patients to take part in the results reporting or dissemination.

### Statistical methods

All statistical analyses will be performed using SPSS Statistics for Windows V21.0 (IBM SPSS). Three sets of data will be used:Full analysis test (FAS). This will include all randomized cases that underwent assessments at least once for efficacy analysis. Missing data, which may affect analysis, will be supplemented using the last observation data. FAS will be the main population for efficacy evaluation.The protocol set (PPS, per-protocol set). This will include patients that meet the inclusion criteria specified in the trial protocol, complete all observation period plans, and do not use other drugs or treatment measures that may affect efficacy evaluation during the trial period. Efficacy evaluation will be conducted using the FAS and PPS. PPS is a secondary population for efficacy evaluation.Safety analysis data set (SS, safety set). This will include all cases that use the study drug at least once and undergo post-treatment safety evaluation after randomization. The SS will be the main population for safety evaluation.

All statistical tests will be performed as two-sided, and the statistical significance will be set at *p*<0.05. Quantitative indicators will be described using the mean and standard deviation, maximum value, minimum value, and median; moreover, the classification indicators will be described using the number and percentage. For counting data, two-sample tests (including the Cochran-Mantel-Haenszel test) or Fisher’s exact probability method will be used for between-group comparisons; moreover, measurement data will be expressed as mean and standard deviation. One-way analysis of variance will be used for among-group comparisons; additionally, the least significant difference method (LSD-t test) will be used for between-group comparisons.

Demographics (age, sex, duration of illness, education level) and MMSE scores will be compared between the two groups as baseline assessments. The main time point for efficacy evaluation is 12 treatment weeks (for PPS), as well as when the group is discontinued (for the FAS population). The *t*-test will be used for between-group comparisons of other measured efficacy indicators, including analyzing the change from the baseline. The ADAS-cog, MMSE, ADCS-ADL, and QOL-AD will be analyzed using the covariance analysis model for between-group comparisons with the baseline.

